### Study Assessments and Procedures

#### Safety Assessments

Clinical examination
At screening, during the procedure, and at all follow-up visits, clinical examination of the perianal fistula will visually assess for infection, excess drainage, chronic inflammation, abnormal bleeding, or fibrosis at the external opening. Photographs of the external openings will be taken at screening and all follow-up visits to document healing progress.Patient medical history
At screening, patients meeting inclusion criteria will be screened for exclusion criteria through their medical history. The etiology of the perianal fistula will also be discussed and documented. Participants will review any known allergies, previous surgical procedures, previous complications, and frequency of fistula occurrence or recurrence.Pregnancy test
At screening, women of childbearing potential will be required to take a pregnancy test and must agree to use two reliable contraceptive methods for the duration of their participation in the study, one of which must be a barrier method; the contraceptive methods will be documented in the screening eCRFs.Crohn’s Concomitant Medications
At screening and all follow-up visits, Crohn’s medications will be documented for patients with CD-related perianal fistulas, including medication name, single dose amount, route, frequency, start date, and end date.Participant survey
At screening, baseline, and weekly following the procedure till Month 3, participants will complete a self-report questionnaire assessing the frequency and severity of pain, incontinence, and other perianal fistula-related symptoms. If symptoms are increasing in frequency and severity, an off-cycle clinical visit will be scheduled to address any adverse events.Assessment of adverse events
The following adverse events will be recorded in the eCRFs and followed until resolution:
Adverse events that are classified as related to study procedures (that is, potentially-, probably-, or definitely related to study procedures or of uncertain relationship to study procedures), regardless of severitySerious adverse events regardless of relatedness to study procedures.Clinical adverse events, events diagnosed as clinical conditions, with a severity grade ≥ 3, regardless of relatedness to study procedures.

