#### Secondary outcomes

The secondary outcomes of this study will be used to assess the preliminary safety and efficacy of rhPDGF-enhanced collagen for treatment of complex perianal fistulas. A quantitative and descriptive summary of all intervention-related adverse events (AEs) within 3 months of the procedure will be used to assess preliminary safety. Clinical evaluation of fistula healing assessed as healed/not healed by no drainage/drainage from the external opening at the Month 3 follow-up visit will determine the proportion of fistulas healed. Rate of recurrence is assessed by the number of participants with clinically diagnosed healed fistulas (no drainage/no leakage) that are later diagnosed with recurrence at the final, Month 6 study visit. The Month 6 endpoint was chosen because successful treatment of complex perianal fistulas is based not only on a diagnosis of being completely healed by clinical exam but also on clinical remission without recurrence, and the majority of recurrences occur within 6 months of the treatment. Safety and efficacy will also be assessed by the change in patient-reported pain, incontinence, and other perianal fistula-related symptoms in the baseline and weekly follow-up participant surveys.

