### Risks

The inclusion and exclusion criteria for this study were designed to minimize the risks to participants receiving rhPDGF-enhanced collagen for treatment of complex perianal fistulas in this study. Given that the intervention will be implanted at baseline and the rhPDGF will be released and metabolized over the first 2–3 days, we do not anticipate any long-term risks. The plethora of human safety data that is published supports the expectation that the only risks involved with the use of rhPDGF is the potential to increase acute inflammation at the site of application following intervention. There is the possibility of erythematous at the site of application due to the accumulation of blood in dilated capillaries during the initial healing phases, but these are also the primary symptoms associated with the presence of an anal fistula. The only other risks are associated with routine care procedures. The use of a commercially available collagen plug is one type of routine care procedure with a success rate of approximately 50%. The collagen matrix used in the intervention arm of the study will be saturated with rhPDGF to potentially enhance healing and improve the success rate. Throughout the life cycle of the study, safety assessments will be used to ensure proper monitoring of adverse events. Safety assessments will consist of clinical examinations, evaluation of patients’ medical history, pregnancy testing, identification of concomitant medication taken due to CD, and weekly participant surveys. The potential benefits of this investigational intervention to improve the healing rates, time in remission, and quality of life outweigh the minimal risks in individuals with complex perianal fistulas.

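### Non-serious grade 1-2 local events judged unrelated to study procedures are not recorded as adverse events, so the mild-reaction count rests on an attribution that the adverse-event record cannot check

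*Protocol article*

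**What the plan says.** The Safety Assessments section (assessment of adverse events) states: "The following adverse events will be recorded in the eCRFs and followed until resolution". Three categories follow.

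- The first is "Adverse events that are classified as related to study procedures". It is defined widely: potential, probable, definite and uncertain relations all count, at any severity.
- The second is serious adverse events, whatever the relation.
- The third is clinical events "with a severity grade ≥ 3, regardless of relatedness to study procedures".

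The Risks section says that "the only risks involved with the use of rhPDGF is the potential to increase acute inflammation at the site of application". It adds that redness may occur in early healing, and remarks that "these are also the primary symptoms associated with the presence of an anal fistula".

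Under Secondary outcomes, the safety endpoint is restricted by relatedness: "A quantitative and descriptive summary of all intervention-related adverse events (AEs) within 3 months of the procedure will be used to assess preliminary safety". The Secondary and Tertiary Outcomes Analysis section then compares the proportion of participants with treatment-related events between arms by Fisher's exact test.

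**The concern.** A filter on relatedness does little harm where attribution is easy. Here the expected product reaction has the same appearance as the disease. A mild local reaction that the assessor puts down to the fistula is not entered as an adverse event, and the endpoint counts only related events. No unfiltered adverse-event record is left against which that judgement could be tested.

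Attribution may also differ by arm. A participant with a collagen implant and a participant with Crohn's disease who had only seton removal and debridement may show the same redness and be classified differently. The Fisher comparison would then partly reflect attribution. The direction is open: attributing events to the fistula in treated participants would lower their count, and doing so more readily in controls without an implant would make the intervention look worse.

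At stake is the preliminary safety description that is meant to guide a larger trial. Mild events that are not entered at the time are hard to reconstruct later.

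**Working it through.** The plan gives no expected rate of adverse events, so there is no figure of its own to reproduce. The check is mainly a reading of the sections side by side.

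**1. Which events fall outside the list**

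| Event | Classified as related, potentially related or uncertain | Classified as unrelated |
|---|---|---|
| Serious, any grade | recorded | recorded |
| Clinical event, non-serious, grade 3 or higher | recorded | recorded |
| Non-serious, grade 1-2 | recorded | **not recorded** |

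Only the last cell is empty. A reaction that resembles the fistula is lost from the adverse-event record only if it is positively classified as unrelated.

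**2. What each arm receives**

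Randomization and Blinding expects 9 participants with Crohn's disease and 3 idiopathic participants, in blocks of three at 2:1. That gives 9 × 1/3 = 3 Crohn's controls and 3 × 1/3 = 1 idiopathic control. Under Efficacy Assessments, Crohn's controls have seton removal and debridement without an implant. So 3 of 4 controls are expected to have no implant, while all 8 intervention participants have one.

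**3. What the back-up holds**

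- *Examinations and photographs.* These take place at all follow-up visits, and the first is at Month 1 (Trial design). The Risks section says rhPDGF is released and metabolized over the first 2-3 days, so an early transient reaction may have gone by then. The safety examination names chronic inflammation. The efficacy examination names local inflammation, for judging healing.
- *Weekly surveys to Month 3.* These cover pain, incontinence and fistula symptoms, and are analysed by arm whatever the attribution. As described, they carry no adverse-event grade or relatedness. Worsening symptoms lead to an unscheduled visit, but an event found there passes through the same list.

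**4. Illustration of size (assumed values)**

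Let p be the true rate of mild local reactions, m the share of them judged unrelated, and n = 8 (Sample Size). Both p and m are assumptions.

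Expected number recorded = 8 × p × (1 − m). Chance that none is recorded = [1 − p(1 − m)]^8. For p = 0.25 and m = 0.5 this is (1 − 0.125)^8 = 0.875^8 = 0.34.

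| p | m = 0 | m = 0.5 | m = 0.75 |
|---|---|---|---|
| 0.125 | 34% | 60% | 78% |
| 0.25 | 10% | 34% | 60% |
| 0.50 | 0.4% | 10% | 34% |

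At p = 0.25 the expected numbers recorded are 2.0, 1.0 and 0.5. A result of 0/8 has a Clopper-Pearson upper limit of 1 − 0.025^(1/8) = 0.37. That interval covers sampling error only, not misattribution.

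**5. What a change in recording would do**

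Suppose 4 of 8 treated participants have a mild local reaction and 2 are judged unrelated (assumed).

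| Plan | Related-event endpoint | All local events |
|---|---|---|
| As written | 2/8 = 25% (95% CI 3-65%) | not available |
| Wider recording only | 2/8 = 25% (3-65%) | recorded, not reported |
| Wider recording and a by-arm summary | 2/8 = 25% (3-65%) | 4/8 = 50% (16-84%) |

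The gap between 25% and 50% comes from the attribution. The recording rule decides whether anyone can see it.

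**The case against.** The strongest reply is that the first category is wide. It takes in potential and uncertain relations at any grade, and the relation is to study procedures, not to rhPDGF alone. Those procedures include seton removal and debridement of the tract in every arm. Redness a few days after debridement is at least potentially related in either arm, so an assessor would have to rule out any link before the event was lost. This stands, and it should keep the lost share small if the category is applied as written. It does not make the share zero or checkable.

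The restricted record also matches the restricted endpoint, so the sections do not contradict each other. That stands too: this is a weakness of design. The full protocol and SAP are not shown and may hold rules on worsening from baseline or on who judges relatedness. If blinded staff make that judgement, a difference by arm is less likely.

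A reader might infer three stronger things that the article does not support.

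- That mild events are never recorded, or disappear from the safety data. Serious events are recorded at any grade, and examinations, photographs and surveys keep some of the information.
- That the protocol itself calls the attribution difficult. It says only that the symptoms are shared; the difficulty is an inference, though a fair one.
- That the recording rule alone halves the reaction rate. In step 5 the related-event figure is the same with or without wider recording.

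**Conclusion.** The concern holds in a limited form. Non-serious grade 1-2 events classified as unrelated to study procedures are not entered as adverse events. Because the expected local reaction shares the fistula's primary symptoms, the endpoint counts related events only, and most controls are expected to have no implant, the count of mild local events depends on an attribution that may differ by arm and cannot be checked from the adverse-event record.

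The size is unknown. Step 4 shows how it varies with p and m, neither of which the article gives, and the wide definition of related events should lower m. No figure stated in the article changes. The primary outcome counts only intervention-related serious events, and serious events are always recorded, so it is unaffected. The change is worth making because it is cheap and the trial is still collecting data.

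**What to change.** Two changes are needed together.

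1. In Safety Assessments, record every perianal or application-site adverse event of any grade, from the procedure to Month 3, in both arms and whatever its attribution. Hold relatedness as a separate field. The present list can stay for events away from the application site.
2. In Secondary and Tertiary Outcomes Analysis, add a by-arm summary of all such local events regardless of relatedness, beside the related-event endpoint. Without this, the first change alters no reported result.

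Since enrollment began in November 2024, state the date from which the wider rule applies and report which participants it covers.

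The cost is an amendment to the protocol and the case report form, and some extra entries for 12 participants. Unless worded otherwise, the added events would also come under the existing requirement for follow-up to resolution. The reported number of mild local events will be higher, and some of them will be fistula symptoms, so the two summaries should be read side by side.

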#### Efficacy Assessments

Clinical examination
At screening, baseline, and all follow-up visits, clinical examination of the perianal fistula will visually assess drainage, local inflammation, and epithelialization at the external opening to determine if the fistula is healed. Photographs of the external openings will be taken at screening and all follow-up visits to document healing progress.Baseline Participant Survey
At consenting, participants will complete a self-report questionnaire to assess:
Perianal fistula-related symptomsPain scaleWexner Incontinence ScaleFollow Up Participant Survey
Following the baseline procedure till the Month 3 follow-up visit, participants will complete a weekly self-report questionnaire to assess:
Perianal fistula-related symptomsPain scaleIncontinence (adapted from Wexner Incontinence Scale)Study Intervention – Baseline or Crossover
Seton removal, debridement of fistula tract, and implantation of the rhPDGF-BB-enhanced collagen plugStudy Control – Baseline only
Seton removal and debridement of fistula tract – Routine care for CD-related complex perianal fistulasSeton removal, debridement of fistula tract, and implantation of the commercially available anal fistula plug – Routine care for idiopathic complex perianal fistulas

### Participant Discontinuation/Withdrawal from the Study

Participants are free to withdraw from participation in the study at any time upon request. An investigator may discontinue or withdraw a participant from the study for the following reasons:

Failure to heal by the Month 3 follow-up visitInfection or abscess which requires discontinuation of the study intervention by removal of the collagen plug followed by a routine care procedureUnacceptable adverse event(sIn the judgement of the investigator, further treatment would not be in best interest of patientSubstantial non-compliance by the patient with the requirements of the studyThe patient uses illicit drugs that may have reasonable chance of interfering with resultsPatient is lost to follow-upDevelopment of intercurrent illness or situation which would affect assessments of clinical status and study endpoints to a significant degreePregnancy
In the event a study participant becomes pregnant prior to the Month 3 follow-up visit, the pregnancy will be followed to delivery and maternal and fetal outcomes will be documented.IncarcerationDisease progression which requires discontinuation of the study interventionParticipant meets an exclusion criterion (either newly developed or not previously recognized) that precludes further study participation

### Risks

The inclusion and exclusion criteria for this study were designed to minimize the risks to participants receiving rhPDGF-enhanced collagen for treatment of complex perianal fistulas in this study. Given that the intervention will be implanted at baseline and the rhPDGF will be released and metabolized over the first 2–3 days, we do not anticipate any long-term risks. The plethora of human safety data that is published supports the expectation that the only risks involved with the use of rhPDGF is the potential to increase acute inflammation at the site of application following intervention. There is the possibility of erythematous at the site of application due to the accumulation of blood in dilated capillaries during the initial healing phases, but these are also the primary symptoms associated with the presence of an anal fistula. The only other risks are associated with routine care procedures. The use of a commercially available collagen plug is one type of routine care procedure with a success rate of approximately 50%. The collagen matrix used in the intervention arm of the study will be saturated with rhPDGF to potentially enhance healing and improve the success rate. Throughout the life cycle of the study, safety assessments will be used to ensure proper monitoring of adverse events. Safety assessments will consist of clinical examinations, evaluation of patients’ medical history, pregnancy testing, identification of concomitant medication taken due to CD, and weekly participant surveys. The potential benefits of this investigational intervention to improve the healing rates, time in remission, and quality of life outweigh the minimal risks in individuals with complex perianal fistulas.

### Statistical analysis

Categorical and binary data will be presented using counts and percentages. Continuous data will be presented using medians and interquartile ranges. All statistical tests will use an α = 0.05 Type I error rate, using two-tailed p-values as appropriate for the specified hypotheses, but 95% confidence intervals will be given primary focus above p-values (29). Statistical models will be adjusted for Crohn’s status. Model assumptions will be checked using visualizations and tests as appropriate, with data transformations and alternative models considered when assumptions are dubious.

#### Sample Size

This study will aim to recruit and screen 60 eligible patients to enroll and randomize 12 participants in a 2:1 ratio. Sample size was influenced by expected confidence interval widths for the primary outcome (technical performance of the rhPDGF-BB-enhanced collagen implant for treatment of complex perianal fistulas). Assuming that all 8 participants assigned to the intervention arm will achieve successful implementation of the treatment, the lower bound of a Clopper-Pearson 95% confidence interval would be 0.63, indicating high confidence that the treatment does not have a low probability of successful implementation. Sample size was also influenced by the efficacy outcome of healing at 3 months. Based on the prior work in the literature, we assume that the routine care arm (across the expected distribution of routine care procedures) will achieve 50% healed at 3 months (2/4 healed). If 7 of the 8 intervention arm patients achieve healing, the expected lower bound of a Carlin-Louis 95% confidence interval for the differences in proportions healed would be about −0.14, indicating high confidence that the intervention does not cause substantial harm. Furthermore, if all 8 intervention arm patients achieve healing, the expected interval lower bound will be −0.01, such that there is high confidence of treatment benefit.

We assumed that study dropout before Month 3 will not occur, and that crossover into the intervention arm will not occur until after ascertainment of Month 3 outcomes. The time-to-healing will be considered for secondary analyses and likely have slightly higher power assuming that patient-reported data is accurate and high quality, as it achieves higher granularity to assess healing than the binary outcome of healing at Month 3 follow-up. Likewise, exploratory analyses including crossover patients may improve power for assessing the primary outcome. Other secondary endpoints and subgroup analyses are exploratory in nature, and we did not perform formal power analyses for these.

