#### Secondary and Tertiary Outcomes Analysis

The secondary efficacy and safety endpoints will be analyzed for all randomized participants, as appropriate. Analyses will not be dependent on the findings of the primary endpoint. The first secondary endpoint considers all treatment-related adverse events and the proportion of participants with such events by arm will be analyzed/reported in the same way as the primary endpoint. The proportion will then be compared across arms using Fisher’s Exact test. If there are at least two participants with multiple treatment-related adverse events, a Mann-Whitney test will compare the number of adverse events per participant across arms.

The next secondary endpoint is fistula healing at Month 3 measured as a binary variable. The probability of healing in each arm will be calculated as the proportion of randomized participants per arm that are diagnosed as completely healed by a clinical evaluation of no visible drainage from the external opening at the Month 3 follow-up visit. The endpoint will be modeled as the outcome in a logistic regression model, conditioning on the treatment arm and baseline etiology. The effect will be presented as an adjusted odds ratio with a 95% confidence interval, as well as the marginal risk ratio after performing standardization. A p-value less than 0.05 will be considered statistically significant, but interpretation will be primarily focused on the 95% confidence interval. Residuals will be inspected to inspect model fit and validity of the homoscedasticity assumption. If model fit is poor, a Fisher’s Exact test will be used in place of logistic regression. Missing data are expected to be limited but will be handled using multiple imputation. Individuals who are lost to follow-up before Month 3 will also be included via the multiple imputation procedure, considering plausible imputations conditional on their baseline and Month 1 follow-up assessments, as well as weekly symptom data. The primary analysis will be modified intention-to-treat (ITT) based on randomized arm, as the investigational product is not available to patients who are not randomized to treatment before the Month 3 outcome assessment. It will be modified ITT in the sense that only participants who receive the investigational intervention will be analyzed as part of the intervention arm; this is necessary as some exclusion criteria cannot be assessed until the time of surgery.

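### The Month 3 healing precision in the sample size section is a Carlin-Louis interval for a risk difference, which no analysis in the document reports

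*Protocol article*

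**What the plan says.** **Sample Size.** The plan is to "enroll and randomize 12 participants in a 2:1 ratio", so 8 v 4. The primary outcome comes first (8/8 successes, Clopper-Pearson lower bound 0.63). Month 3 healing is named as a further influence, with control healing taken as 2/4. Its precision is expressed only as the "expected lower bound of a Carlin-Louis 95% confidence interval for the differences in proportions healed", about −0.14 for 7/8 healed on intervention and −0.01 for 8/8. The first bound is read as strong assurance against substantial harm and the second as strong assurance of benefit.

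**Secondary and Tertiary Outcomes Analysis.** The same endpoint goes into a logistic regression on arm and etiology. "The effect will be presented as an adjusted odds ratio with a 95% confidence interval", together with a marginal risk ratio from standardization. If fit is poor, a Fisher's "Exact test will be used in place of logistic regression".

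**Statistical analysis.** The general policy is that "95% confidence intervals will be given primary focus above p-values". The healing paragraph repeats that emphasis.

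**Where Carlin-Louis is planned.** It is named for the primary endpoint, which is a single proportion. Adverse-event proportions by arm and retention proportions follow that method. Recurrence follows the healing analysis.

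**The concern.** A precision statement in a sample size section tells the reader how tight an answer to expect from the planned analysis. Here it describes a different quantity: an unadjusted Bayesian interval on the difference scale, where the plan has adjusted ratio measures. Neither of the two conclusions drawn from the bounds can then be checked against a planned result.

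The mismatch also matters in the sponsor's own scenarios. With 8 v 4 participants and high healing on intervention, maximum-likelihood logistic regression is prone to separation. The analysis may then fall back on a p-value in the very result that the sample size section treats as the most favourable.

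**Working it through.** **Inputs.** 8 v 4 participants, control 2/4, intervention 7/8 or 8/8, and no dropout before Month 3 (Sample Size). Two-sided 95% (Statistical analysis). For the adjusted model: 9 Crohn's and 3 idiopathic participants in blocks of 3 (Randomization and Blinding), so with complete blocks 6 v 3 and 2 v 1.

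**1. The stated bounds.** The prior is not given. With independent uniform priors and equal tails, the posteriors are Beta(healed + 1, not healed + 1):

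| Scenario | Posteriors | 95% interval for the difference | Stated lower bound |
|---|---|---|---|
| 7/8 v 2/4 | Beta(8,2) v Beta(3,3) | −0.145 to 0.717 | about −0.14 |
| 8/8 v 2/4 | Beta(9,1) v Beta(3,3) | −0.008 to 0.788 | −0.01 |

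Both reproduce. Jeffreys priors give −0.130 and +0.037, highest-density intervals −0.129 and +0.009, and Newcombe −0.117 and +0.023. None of these matches both figures, so the sizing interval is identified.

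**2. The planned analysis at 7/8 v 2/4.**
- Unadjusted OR = (7 × 2)/(1 × 2) = 7.0. SE(log OR) = √(1/7 + 1/1 + 1/2 + 1/2) = 1.464. Wald 95% CI 0.40 to 123.
- Unadjusted RR = 0.875/0.50 = 1.75. SE(log RR) = √(1/7 − 1/8 + 1/2 − 1/4) = 0.518. CI 0.63 to 4.83.
- Fisher p = (48 + 4)/220 = 0.24.

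With the etiology term, four placements of the failures are possible:

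| Intervention healed (CD, idiopathic) | Control healed (CD, idiopathic) | Adjusted OR (Wald 95% CI) |
|---|---|---|
| 5/6, 2/2 | 2/3, 0/1 | 7.3 (0.39 to 134) |
| 6/6, 1/2 | 1/3, 1/1 | 7.3 (0.39 to 134) |
| 5/6, 2/2 | 1/3, 1/1 | 10.0 (0.40 to 250) |
| 6/6, 1/2 | 2/3, 0/1 | not finite |

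In the last row the likelihood keeps rising as the arm and etiology coefficients grow together and the intercept falls by the same amount. The two mixed cells keep their fit, and the other two approach 100% and 0%.

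**3. The planned analysis at 8/8 v 2/4.** Every intervention participant heals, so the arm coefficient has no finite maximum in either placement of the control successes (2/3 and 0/1, or 1/3 and 1/1). Fisher p = C(4,2)/C(12,2) = 6/66 = 0.091. The sizing interval on the same data is finite, −0.008 to 0.788.

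**4. Side by side.** Sizing uses a difference with a Carlin-Louis interval. The analysis uses an adjusted odds ratio, a standardized risk ratio and a Fisher fallback. No section of the document links the two.

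**The case against.** The other side has real points.

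- **The SAP and standardization could supply the difference.** Per-arm healing proportions will be reported, and standardization yields two marginal risks, so a point difference can be derived. The SAP, not shown here, may add an interval. The claim is therefore limited to the analyses in this document. It remains a mismatch between two things the article states, since the effect measures and the fallback are both spelled out.
- **Limits can exist at 8/8.** Wald limits are not specified. The profile-likelihood lower limit for the OR is 1.8 unadjusted and 2.2 or 2.9 adjusted, the exact conditional limit is 0.42, and an unadjusted RR is 2.0 (0.75 to 5.33: SE = √(1/2 − 1/4) = 0.5). It would be wrong to say that no interval is possible. But these lower limits fall on both sides of 1, and the document does not choose among them. It also allows alternative models when assumptions are dubious, but names only Fisher's test for poor fit.
- **The sample size does not depend on this.** A reader might infer that N = 12 was chosen to support the no-harm statement. The text does not say so: the primary outcome comes first, healing only also influenced N, and the Discussion cites case-counts and concedes limited power for efficacy.
- **The loss of precision cannot be put in percentage points.** A reader might convert the ratio limits to risks at 50% control healing, get −0.22 (OR 0.40) and −0.18 (RR 0.63), and conclude that 4 to 8 points are lost against −0.14. That is not like for like. It fixes the control risk, while the difference interval lets both arms vary. Converting the sizing posterior itself in this way gives −0.18 by its OR limit (0.46) and −0.10 by its RR limit (0.81), so much of the gap comes from the conversion.
- **An unadjusted headline is debatable.** The protocol adjusts models for Crohn's status, and the control procedure differs by etiology. That speaks against replacing the adjusted estimates, but not against adding the difference.

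**Conclusion.** The point holds as a mismatch between the sizing and the analysis of Month 3 healing. The bounds −0.14 and −0.01 are arithmetically right but describe an interval that no analysis in this document reports.

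Its practical size is this. At 8/8 v 2/4 the planned maximum-likelihood model gives no finite odds ratio in either placement. At 7/8 v 2/4 this happens in one of four placements. The named fallback is then a p-value (0.09 at 8/8) with no stated interval, which sits badly with the interval-first policy.

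This rests on three assumptions: an ordinary maximum-likelihood fit, the expected 9/3 etiology split with complete blocks, and uniform priors for the Carlin-Louis interval. Separation at 8/8 does not depend on the split or the priors. The finding does not overturn N = 12 and does not establish a shortfall in percentage points.

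**What to change.** In Secondary and Tertiary Outcomes Analysis, add the difference in proportions healed at Month 3 (intervention minus control) with its Carlin-Louis 95% interval. State the uniform priors and equal tails that reproduce the Sample Size figures. Report it whatever the logistic model does, alongside the etiology-adjusted odds ratio and the risk ratio rather than in their place. The SAP should say how the interval is formed if a Month 3 outcome is multiply imputed.

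If the sponsor does not want this estimate, state in Sample Size that −0.14 and −0.01 do not describe the planned odds-ratio analysis, and remove the two confidence statements drawn from them.

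The cost is a sentence or two in the protocol and SAP and a few lines of code, with no extra participants or data. The trial is described as ongoing, so this can be settled before results are known. One small drawback is that the added interval is not adjusted for etiology. Stratified 2:1 blocks limit imbalance, but incomplete blocks or the modified intention-to-treat exclusions could still produce some, which is why the adjusted estimates should stay beside it.
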